# Rationale and design of the HepZero study: a prospective, multicenter, international, open, randomized, controlled clinical study with parallel groups comparing heparin-free dialysis with heparin-coated dialysis membrane (Evodial) versus standard care: study protocol for a randomized controlled trial

**DOI:** 10.1186/1745-6215-14-163

**Published:** 2013-06-01

**Keywords:** Hemodialysis, Heparin-free, Evodial, Randomized controlled trial

## Abstract

**Background:**

Anticoagulation for chronic dialysis patients with contraindications to heparin administration is challenging. Current guidelines state that in patients with increased bleeding risks, strategies that can induce systemic anticoagulation should be avoided. Heparin-free dialysis using intermittent saline flushes is widely adopted as the method of choice for patients at risk of bleeding, although on-line blood predilution may also be used. A new dialyzer, Evodial (Gambro, Lund, Sweden), is grafted with unfractionated heparin during the manufacturing process and may allow safe and efficient heparin-free hemodialysis sessions. In the present trial, Evodial was compared to standard care with either saline flushes or blood predilution.

**Methods:**

The HepZero study is the first international (seven countries), multicenter (10 centers), randomized, controlled, open-label, non-inferiority (and if applicable subsequently, superiority) trial with two parallel groups, comprising 252 end-stage renal disease patients treated by maintenance hemodialysis for at least 3 months and requiring heparin-free dialysis treatments. Patients will be treated during a maximum of three heparin-free dialysis treatments with either saline flushes or blood predilution (control group), or Evodial. The first heparin-free dialysis treatment will be considered successful when there is: no complete occlusion of air traps or dialyzer rendering dialysis impossible; no additional saline flushes to prevent clotting; no change of dialyzer or blood lines because of clotting; and no premature termination (early rinse-back) because of clotting.

The primary objectives of the study are to determine the effectiveness of the Evodial dialyzer, compared with standard care in terms of successful treatments during the first heparin-free dialysis. If the non-inferiority of Evodial is demonstrated then the superiority of Evodial over standard care will be tested. The HepZero study results may have major clinical implications for patient care.

**Trial registration:**

ClinicalTrials.gov NCT01318486

## Background

Hemodialysis treatment requires anticoagulation, usually with unfractionated or low molecular weight heparin to prevent thrombosis of the dialyzer and the extracorporeal circuit (dialyzer and blood lines or cassette system). In clinical practice, it is not unusual to perform hemodialysis for patients with active bleeding or increased bleeding risk conditions when heparin anticoagulation is contraindicated. Various solutions have been attempted to prevent clotting of the extracorporeal circuit.

Heparin-free dialysis using intermittent saline flushes is widely adopted as the method of choice for patients at risk of bleeding [1,2] and is currently recommended by the European Best Practice Guidelines in hemodialysis (2002) [3], although the level of evidence is somewhat weak since no randomized controlled studies evaluating this method have been reported to date [4-11]. Heparin-free treatment with on-line predilution rather than regular saline flushes is also a technique used at some dialysis units. Saline infusion is far from optimal for several reasons, including an increased volume load that would need to be removed with dialysis and an added logistic burden on dialysis nurses, owing to the need for close one-to-one nursing in cases of intermittent boluses [1]. In addition, this technique is still associated with clotting risks (15% to 35%, depending on the literature) which, in addition to blood loss, may reduce the efficiency of a dialysis session that has to be stopped frequently or prematurely. Regional (heparin administration into the arterial line and protamine into the venous line) or tight heparinization (use of minimal dose of heparin) is not recommended for patients with active bleeding or at risk of bleeding [3]. Indeed, although these methods lower the risk of bleeding compared to the standard method, there is still a notable risk of bleeding (5% to 50%) [12].

The use of regional citrate anticoagulation (RCA) is limited by the need for additional equipment (additional pumps for citrate and calcium), the potential risk of deterioration of electrolyte and acid–base equilibrium (hypocalcemia, hyponatremia) requiring close monitoring of electrolytes [12], and a need for clotting time evaluation since the risk of bleeding is reduced but may still occur. Recently, the feasibility of anticoagulating the extracorporeal circuit during hemodialysis using a simple citrate-enriched dialysate was evaluated in a pilot (no prespecified sample size calculation or primary endpoint), monocentric, prospective, randomized, crossover study of 24 patients with high risk of bleeding [13]. For anticoagulation of the extracorporeal circuit, one treatment used the citrate-enriched dialysate (citrate group), while the other treatment used conventional saline flushing (saline group). With either method, a heparinized, saline-rinsed polyamide dialyzer was used and no heparin was administered during dialysis. Ninety-two per cent (22 out of 24) and 100% of patients tolerated the procedure well in the citrate group and saline group, respectively. Eight per cent (two out of 24) of the treatments in each group had to be abandoned because of clotting in the extracorporeal circuit, while significantly less thrombus formation in the venous air traps was detected in the citrate group [13]. Other alternatives such as prostacyclin are costly and require close hemodynamic monitoring [3]. In a pilot (without sample size calculation or prespecified primary endpoint), monocentric, randomized, controlled trial, Yixiong *et al*. recently compared heparin-free saline flushes with low-dose argatroban (a direct thrombin inhibitor) in a total of 80 hemodialysis sessions performed in 52 patients with high risk of bleeding. They observed a three-fold decrease in major clotting with argatroban (*P* <0.05), without safety issues [14].

Another alternative for heparin-free hemodialysis is to coat heparin on the hemodialyzer hollow fibers [1,12]. Stamatiadis *et al*. reported the results of 16,954 sessions performed with patients bleeding or at risk of bleeding (15,730 retrospectively and 1,224 prospectively collected), with a method combining a priming of two types of hollow fiber wet dialyzers (ethylene vinyl alcohol and polyethylene glycol-coated membranes with 1 liter of saline containing 5,000 IU of unfractionated heparin). After initiation of the treatment, except for hourly rinsing with 50 ml normal saline to inspect the circuit (100 ml for a 3-hour session), no other special nursing attendance was applied. Cumulative failure of treatment, as defined by clotting of the extracorporeal circuit requiring termination of the procedure or replacement of the clotted part, was not greater than 5% [15].

Gambro (Lund, Sweden) have for several years developed coated hemodialyzers such as Nephral ST that are equipped with a membrane, the surface of which is treated with polyethyleneimine (PEI) allowing extemporaneous coating with heparin when the hemodialyzer is primed with saline solution containing heparin. Several clinical studies have been performed with Nephral ST to demonstrate the possibility of decreasing systemic heparin doses or of even performing hemodialysis treatments without heparin [16-18]. In a study aimed at evaluating the AN69 ST membrane in heparin-free dialysis in patients at risk of bleeding (n = 68) less than 2% massive clotting were observed (6 out of 331 dialysis sessions) [17]. Evenepoel *et al*. performed a monocenter, prospective, randomized trial including 33 hemodialysis patients at high risk of bleeding, in whom regional anticoagulation was achieved by means of either AN69 ST (Nephral ST; 11 patients, 31 sessions), RCA-Ca0 (11 patients, 32 sessions) or RCA-Ca3.0 (11 patients, 30 sessions). Clotting phenomena necessitating premature termination of the dialysis session were encountered in 39%, 13% and 0% using AN69 ST, RCA-Ca3.0 and RCA-Ca0, respectively (*P* <0.005). The authors concluded to the superiority of citrate regional anticoagulation [19]. In a bicentric, Austrian, randomized, crossover trial, Kodras *et al*. treated 10 patients receiving oral anticoagulants with AN69 ST and FX 100 (a polysulfone membrane) for 1 week (total 30 sessions of heparin-free dialysis, with only priming of the dialyzer and no systemic heparinization). Changes of clotting markers, occurrences of complete thrombosis and Kt/V were similar with both membranes [20]. More recently, a prospective, randomized, crossover study examined 10 stable patients during intermittent hemodialysis with: 1. regular saline flushes of extracorporeal circuit; 2. RCA; and 3. AN69 ST membrane after extracorporeal circuit priming. All 10 procedures with RCA were successfully completed after 4 hours, whereas six out of 10 procedures with saline flushes and five out of 10 procedures with AN69 ST were terminated prematurely because of clotting (*P* <0.05). Due to insufficient statistical power of the negative results, the number of incomplete procedures did not allow the authors to directly compare saline flushes and AN69 ST [21].

A new dialyzer, Evodial (Gambro), which is an upgrade of the Nephral ST dialyzer, is grafted with unfractionated heparin during the manufacturing process. *In vitro* and *in vivo* data requested for CE marking have shown the stability of heparin grafting. Several clinical studies have been performed with Evodial [22,23]. A 30% heparinization reduction with Evodial dialyzers led to an improvement in oxidative stress, thereby testifying an effective biocompatibility [22]. In a study performed in 45 chronic dialysis patients, Kessler *et al*. have shown that the systemic heparin dose, regardless of heparin type (unfractionated heparin or low molecular weight heparin), can be reduced by 45% ± 13% without any coagulation issues, which was defined as very early clotting signs such as quality of rinse-back in the circuit (dialyzer and blood lines) [18].

The present HepZero study hypothesis is that in patients requiring heparin-free dialysis, the heparin-free treatment with Evodial can be easily performed (without saline flushes or blood predilution) and is at least not inferior and may be superior to the standard care heparin-free treatment in terms of clotting, as assessed for the first time by an international, multicenter, randomized, controlled, open-label trial with two parallel groups.

## Methods/Design

### Study design

This clinical study is a prospective, multicenter (10 centers), international (7 countries), open, controlled, randomized clinical study (Figure 1). Two types of therapies will be evaluated in parallel.

**Figure 1 F1:**
[figure not shown]
Study flow-chart.

The control group will receive heparin-free hemodialysis treatment according to standard care. Since there is no unique standard heparin-free treatment, the control group will receive the usual procedure in place at each study site (saline flushes or predilution) with guidelines aimed at standardizing practices within the control group. The standard care can be either saline flushes during dialysis treatment (100 ml to 300 ml per flush every 30 minutes, as stated in the European Best Practice Guidelines (2000) [3]) or predilution (on-line or bags, with a predilution rate between 1 l/h and 2 l/h; high-volume hemodiafiltration is not allowed).

The study device group will receive heparin-free hemodialysis treatment with Evodial. To allow the comparison, a dialyzer with roughly the same surface area as Evodial 1.6 (1.65 m^2^) will be used in the study group. Consecutive patients will be screened by the investigators and, when eligible, will be enrolled in the study and treated during a maximum of three consecutive heparin-free dialysis treatments, without any switch allowed between arms.

#### Primary objectives

The primary objectives of the study are to determine the effectiveness of the Evodial dialyzer, compared with standard care in terms of successful treatments during the first heparin-free dialysis. If the non-inferiority of Evodial is demonstrated then the superiority of Evodial over standard care will be tested.

#### Secondary objectives

The secondary objectives are: to compare the success rate during the second and third consecutive heparin-free dialysis treatment with Evodial to standard care; to compare clotting grades in air traps during all treatments with Evodial versus standard care; to assess the efficacy of heparin-free dialysis treatment with Evodial versus standard care; to assess the ease of use of heparin-free dialysis treatment with Evodial; and to follow-up the safety of heparin-free dialysis treatment with Evodial versus standard care.

#### Study population

The patients to be included in this clinical study are end-stage renal disease patients treated by maintenance hemodialysis for at least 3 months and requiring heparin-free dialysis treatments. Reasons for heparin-free dialysis prescription will be recorded and may include: gastrointestinal hemorrhage; invasive procedure: pre-, post-procedure; perioperative: pre- or post-surgery; cerebral hemorrhage: type and date; other bleeding risk; other reason not related to bleeding risk; cholesterol emboli; diabetic retinopathy; and other reason.

Bleeding risk will be graded according to the Lohr and Schwab definition [24]: very high risk, active bleeding at time of dialysis; high risk, active bleeding stopped for less than 3 days or surgery or trauma within the previous 3 days; moderate risk, active bleeding stopped for more than 3 days but less than 7 days, surgery or trauma within the previous 3 to 7 days, or uremic pericarditis or pleuritis; and low risk, greater than 7 days after active bleeding, surgery or trauma.

These patients shall meet the following inclusion and exclusion criteria defined for this study. Inclusion criteria are the following: patients requiring heparin-free dialysis treatments as per nephrologists’ prescription; chronic end-stage renal disease patients treated by maintenance hemodialysis for at least 3 months; patients with a well-functioning blood access that can allow a blood flow of at least 250 ml/min; patients aged 18 years or older;written consent to participate in the study (informed consent).

Patients that have already been treated with heparin-free hemodialysis can be included into the study. The first treatment is defined as the first treatment evaluated when the patient is enrolled in the study. Patients with a catheter locked by heparin can be included in the study, although particular attention must be paid to the removal of heparin and the rinsing of the catheter prior to starting the hemodialysis treatment.

Exclusion criteria are the following: patients in intensive care unit settings; acute kidney injury patients; patients dialyzed in self-care, satellite hemodialysis units; patients treated in single needle mode; known heparin contraindication (heparin-induced thrombocytopenia type II); patients requiring blood and other labile blood products (for example fresh frozen plasma, platelets) transfusion during hemodialysis treatment; patients receiving oral anticoagulants (including anti-vitamin K); patients receiving a combination of anti-platelet agents; patients treated with unfractionated or low molecular weight heparin in addition to the dialysis treatment to prevent deep vein thrombosis; pregnant/planning pregnancy and lactating women during the study period; legally-protected adult patients; patients not affiliated with a health insurance system (beneficiary or dependent); participation in other interventional studies during the study period; and patients that have already been included in this study.

Patients will be considered enrolled in the study when the informed consent has been signed. Time zero is when the randomization is done. Withdrawn patients will be replaced only if the patient has been randomized and no dialysis treatment could have been performed or in case of an improper second enrolment of the same patient (the second one being not considered).

### Study endpoints

#### Primary endpoints

In order to evaluate the rate of successful treatments, clotting in the air traps will be scored using a semi-quantitative scale (Figure 2) [13,14,19,20,25,26]: grade 1, no detectable clotting; grade 2, minimal clot formation (presence of fibrinous ring); grade 3, clot formation (up to 5 cm) but dialysis still possible; and grade 4, complete occlusion of air traps or dialyzer rendering dialysis impossible.

**Figure 2 F2:**
[figure not shown]
Visual clotting scale.

The first heparin-free dialysis treatment will be considered successful when there is: no complete occlusion of air traps or dialyzer rendering dialysis impossible (grade 4); no additional saline flushes to prevent clotting; no change of dialyzer or blood lines because of clotting; and no premature termination (early rinse-back) because of clotting.

This evaluation (clotting scoring) will be performed hourly by two independent observers. Depending on the organization at each study site, the evaluation can be performed by two nurses (the nurse in charge of the patient and a second nurse not in charge of the patient) or by the nurse in charge of the patient and a co-investigator. In case of discordance between the two observers or in the eventuality of premature session termination (grade 4), the final decision will be made by a third authorized and trained person (the principal investigator or registered co-investigators).

At each site and prior to the enrolment of patients, an organization will be implemented, and the investigator and all those involved in the study will be trained and certified with regard to scoring.

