## Discussion

Anticoagulation for chronic dialysis patients with contraindications to heparin administration is challenging. The regimens used as alternatives, for example anticoagulation-free dialysis, regional heparinization with protamine, direct thrombin inhibitors, prostacyclin or RCA, encounter considerable limitations. Current guidelines state that in patients with increased bleeding risks, strategies that can induce systemic anticoagulation should be avoided. Treatment strategies that avoid this include no use of anticoagulants with regular flushing or RCA [3]. To date, the use of RCA is restricted to specialized units, since its application is cumbersome [26], because it usually requires additional pumps for citrate and calcium infusions, which are not provided by standard dialysis machines, as well as the need for careful monitoring of electrolytes. These issues not only increase the complexity of the RCA procedure but also the likelihood of complications, the most dangerous being systemic hypocalcemia, since it can cause life-threatening arrhythmias [30]. Therefore, heparin-free dialysis using saline infusion is currently *de facto* considered as the gold standard in patients with high risk of bleeding [1,2] and serves as the control intervention in the present trial. For obvious logistical and technical reasons, the study is conducted as open-label and the primary endpoint could not be assessed blindly. Indeed, neither the predilution process nor the saline flushes can be masked and the dialyzers can easily be differentiated by the nursing staff (different housings, different membrane colors and transparency), since they must be carefully examined during the dialysis treatment and they cannot be completely covered by a label aimed at preventing any differentiation between the two groups. In order to minimize potential bias due to the open-label design, it was decided to have the study primary endpoint: 1. evaluated by the most widespread semi-quantitative clotting scale used in research [13,14,19,20,25,26]; 2. independently rated by two observers; in case of discordance between the two observers or in case of premature session stoppage (grade 4), the final adjudication must be made by a third authorized and trained person (the principal investigator or registered co-investigators); and 3. training and certification of nurses and investigators with regard to grading.

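### A grade 4 session on which both observers agree can be re-decided by an unmasked investigator, while an agreed success is never reviewed: a one-way path on the primary endpoint

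*Protocol article*

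**What the plan says.** In the protocol article, under Study endpoints, Primary endpoints, two observers score clotting every hour on a four-grade scale. The first session is a success only if four conditions all hold: no grade 4, no added saline flush to prevent clotting, no dialyzer or line change for clotting, and "no premature termination (early rinse-back) because of clotting".

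The third-person rule has two triggers, either of which is enough. One is disagreement between the observers. The other is worded "in the eventuality of premature session termination (grade 4), the final decision will be made by a third authorized and trained person", namely the principal investigator or a registered co-investigator. The Discussion repeats the second trigger: "in case of premature session stoppage (grade 4), the final adjudication must be made by a third authorized and trained person". It lists this among the measures chosen to limit bias from the open design, after stating that "the study is conducted as open-label and the primary endpoint could not be assessed blindly".

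No sentence sends a session that both observers count as a success to a third person.

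**The concern.** The second trigger does not depend on disagreement. Two trained and certified observers may both record grade 4, which is a failure by definition, and the result is still handed to one person who can know the arm. An agreed success is left alone. For agreed grade 4 sessions the third person can confirm the failure or remove it, and nothing else.

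Non-inferiority is the first test and the gate to superiority, and it is made on the difference in success rates. Removing the same share of failures from both arms shrinks a true deficit, so even an even-handed adjudicator makes non-inferiority easier to declare. Removing more of them from the Evodial arm acts directly on the estimate.

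**Working it through.** **Inputs from the article** (Justification of sample size; Efficacy analysis, Primary objective): control success 65%, margin 15 points, one-sided 5%, 80% power, 126 per arm. Non-inferiority is declared if the lower limit of the one-sided 95% Wilson-type interval for Evodial minus control exceeds −15%.

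**Assumed, not in the documents:** the shares of all failures that the third person turns into successes, f_E (Evodial) and f_C (control).

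**Step 1. The plan's own figure.** With 65% in both arms, n = (1.645 + 0.842)² × 2 × 0.65 × 0.35 / 0.15² = 6.183 × 0.455 / 0.0225 = 125.03, rounded up to 126 per arm. The stated size reproduces (power at 126: 80.3%).

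**Step 2. Model.** Only failures can change, so recorded success = p + f(1 − p). At the boundary:
- Evodial: 0.50 + 0.50 f_E
- Control: 0.65 + 0.35 f_C

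With equal f the recorded difference is −15(1 − f) points.

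**Step 3. Probability of declaring non-inferiority when the true difference is −15 points.** Exact binomial enumeration over both arms, 126 each, with the lower limit from the two single-arm Wilson intervals combined by Newcombe's method:

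| f_E | f_C | Recorded success | Difference (points) | False non-inferiority |
|---|---|---|---|---|
| 0 | 0 | 50.0% vs 65.0% | −15.0 | 5.5% |
| 5% | 5% | 52.5% vs 66.75% | −14.25 | 6.9% |
| 10% | 10% | 55.0% vs 68.5% | −13.5 | 8.5% |
| 20% | 20% | 60.0% vs 72.0% | −12.0 | 12.9% |
| 2% | 0 | 51.0% vs 65.0% | −14.0 | 7.6% |
| 5% | 0 | 52.5% vs 65.0% | −12.5 | 11.7% |
| 10% | 0 | 55.0% vs 65.0% | −10.0 | 21.5% |
| 5% | 10% | 52.5% vs 68.5% | −16.0 | 3.8% |

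For scale, 126 × 0.50 = 63 Evodial failures are expected at the boundary, and 5% of them is about 3 sessions.

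**Step 4. Where the direction turns.** The recorded deficit exceeds 15 points when 0.35 f_C > 0.50 f_E, that is, when control failures are overturned more than 0.50/0.35 = 1.43 times as often as Evodial failures. The last row is such a case.

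**The case against.** **Re-grading alone does not make a success.** A session moved from grade 4 to grade 3 still fails if it was stopped early because of clotting. The third person would also have to find another cause for the stop, after two observers recorded a full blockage. This stands. It makes overturning less likely, but does not open a route in the other direction.

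**A reader might infer that review of every early stop works one way.** The documents do not support that. If the trigger also covers stops below grade 4, the third person could blame clotting where the observers did not and so turn a success into a failure. The one-way property is strict only for agreed grade 4 sessions.

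**A reader might infer that bias towards Evodial is shown.** It is not. The overturn rates are assumed. Failures through flushes or line changes reach the third person only on disagreement, so a given share of all failures implies a higher rate among reviewed sessions. The largest figures come from unequal overturning, which reflects the open assessment that the Discussion discloses.

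**Review can also correct errors, and uncorrected errors dilute too.** By the same enumeration, if 5%, 10% or 20% of true successes in both arms are wrongly recorded as failures and left so, false non-inferiority is 7.2%, 9.1% or 13.6%. If only control successes are affected (2%, 5%, 10%), it is 8.4%, 14.4% or 29.6%. These rates are assumed as well. The point stands against dropping review of why a session was stopped. It has little force for an agreed grade 4, where two trained observers leave little to correct.

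**Conclusion.** The concern holds for agreed grade 4 sessions. The rule lets an unmasked investigator re-decide an agreed failure while agreed successes are final, and this fits badly with its stated purpose of limiting open-label bias. It is a rule stated twice, not a detail left to another document.

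Its size cannot be fixed from the documents. Under the assumed rates, false non-inferiority rises from 5.5% to between 6.9% and 12.9% with equal overturning, and to between 7.6% and 21.5% with overturning in the Evodial arm only. With no overturning there is no effect, and beyond the 1.43 ratio the effect reverses. Equal overturning would also shrink a true benefit, so it does not help superiority. This is an avoidable risk that should be closed, not evidence that the result is biased.

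**What to change.** In Primary endpoints and in the Discussion:

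1. State that a grade 4 on which both observers agree is final and counts as a failure in the primary analysis.
2. Have the third person decide discordant scores and, where an early stop was not an agreed grade 4, whether clotting was the cause. Say that this decision may go either way.
3. Keep both observers' scores as recorded. Report by arm how many sessions the third person changed, and in which direction.
4. Repeat the non-inferiority test on the observers' unadjudicated results as a sensitivity analysis, with the handling of discordant sessions fixed beforehand.

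**Cost.** Some wording, one table and one extra analysis. Both observers' scores are already made under the plan. The article does not say that both observers also record why a session was stopped, so for stops below agreed grade 4 the sensitivity analysis depends on what was captured. With 245 of 252 patients recruited at submission, the change should be dated and made before results by arm are examined. The downside is small: an occlusion that both observers wrongly grade 4 stays a failure in the primary analysis.
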